## Abstract

**Background:**

Kidney transplantation has improved survival and quality of life for patients with end-stage renal disease. Despite excellent short-term results due to better and more potent immunosuppressive drugs, long-term survival of transplanted kidneys has not improved accordingly in the last decades. Consequently there is a strong interest in immunosuppressive regimens that maintain efficacy for the prevention of rejection, whilst preserving renal structure and function. In this respect the infusion of mesenchymal stromal cells (MSCs) may be an interesting immune suppressive strategy. MSCs have immune suppressive properties and actively contribute to tissue repair. In experimental animal studies the combination of mammalian target of rapamycin (mTOR) inhibitor and MSCs was shown to attenuate allo immune responses and to promote allograft tolerance. The current study will test the hypothesis that MSC treatment, in combination with the mTOR inhibitor everolimus, facilitates tacrolimus withdrawal, reduces fibrosis and decreases the incidence of opportunistic infections compared to standard tacrolimus dose.

**Methods/design:**

70 renal allograft recipients, 18–75 years old, will be included in this Phase II, open label, randomized, non-blinded, prospective, single centre clinical study. Patients in the MSC treated group will receive two doses of autologous bone marrow derived MSCs IV (target 1,5x10^6^, Range 1-2x10^6^ million MSCs per/kg body weight), 7 days apart, 6 and 7 weeks transplantation in combination with everolimus and prednisolone. At the time of the second MSC infusion tacrolimus will be reduced to 50% and completely withdrawn 1 week later. Patients in the control group will receive everolimus, prednisolone and standard dose tacrolimus. The primary end point is to compare fibrosis by quantitative Sirius Red scoring of MSC treated and untreated groups at 6 months compared to 4 weeks post-transplant. Secondary end points include: composite end point efficacy failure (Biopsy Proven Acute Rejection, graft loss or death); renal function and proteinuria; opportunistic infections; immune monitoring and “subclinical” cardiovascular disease groups by assessing echocardiography in the different treatment groups.

**Discussion:**

This study will provide information whether MSCs in combination with everolimus can be used for tacrolimus withdrawal, and whether this strategy leads to preservation of renal structure and function in renal recipients.

**Trial registration:**

NCT02057965.

## Background

Kidney transplantation has improved life expectancy and quality of life for patients with end-stage renal failure. However, despite the impressive improvements in short-term outcome parameters due to better and more potent immunosuppressive drugs, the long-term survival of renal allografts has changed little during the past decades [1]. A number of factors, such as quality of the graft, ischemia/reperfusion (I/R) injury, ongoing cellular and humoral alloreactivity and/ or calcineurin inhibitors (CNI) may adversely affect renal structure causing early tubular atrophy and interstitial fibrosis (IF/TA). CNI have been the cornerstone of immunosuppressive therapy for many years, due to their efficacy in preventing acute rejection. However, CNI have nephrotoxic side effects that can directly contribute to renal dysfunction and compromise long-term outcomes. Consequently, there is a clear need for immunosuppressive regimens that maintain efficacy for the prevention of rejection, whilst preserving renal function and structure. The immune regulatory properties of mesenchymal stromal cells (MSCs) in both cellular and antibody mediated inflammatory models have highlighted their potential to regulate the immune response after solid organ transplantation [2]. In addition, MSCs have been shown to ameliorate I/R injury and to exert reparative properties. The administration of MSCs might be an optimal strategy to facilitate CNI withdrawal and to minimize immune suppression. In addition, both MSCs and everolimus might improve cardiovascular status and this strategy might be an opportunity to reduce the toll of cardiovascular disease following kidney transplantation.

### Mesenchymal stromal cells

MSCs are multi potent cells that can be isolated from the bone marrow (BM) and many other sources. There is currently not a single marker that can distinguish MSCs from other cell types. Functional characterization of MSCs relies primarily on their ability to adhere to plastic and their differentiation potential. The International Society of Cellular Therapy stated that MSCs should bear at least the stromal markers CD73, CD90 and CD105, in addition to the absence of the hematopoietic markers CD14, CD34 and CD45 [3,4]. Important for their possible clinical application is that MSCs are easily isolated as they adhere to plastic and are capable of substantial proliferation and expansion in culture [5]. Another advantage is that MSCs can be cryopreserved with no loss of phenotype or differentiation potential [6].

Several studies suggest that MSCs may play a role in modulation of immune responses as extensively reviewed [7,8]. Indeed, MSCs can down regulate many immune effector functions and have also been found to induce regulatory cells [9,10]. These immune modulatory properties make MSCs especially attractive for potential use in treating disease driven by an immune response, including transplant rejection [7,8,11,12]. In addition, MSCs have been shown to improve tissue damage in response to injury. In animal models, MSC administration decreased fibrosis in the heart [13], and other organs such as the lung, liver and kidney [14-18]. Several cytokines have been shown to mediate the anti-fibrotic properties, including BMP-7 [18] and HGF [19]. In addition, various models have shown reparative properties in cardiovascular disease [20]. This is of importance for transplant recipients since cardiovascular disease causes significant morbidity and mortality in these patients. Different studies have suggested that the capacity of MSCs to produce paracrine factors plays a prominent role in affecting tissue repair and immune modulation [11,21].

### Mesenchymal stromal cells and solid organ transplantation

Beneficial immune modulatory effects of MSCs have been shown in experimental models of allo immune disorders. In the case of solid organ transplantation, the use of MSCs for several indications have been tested, including treatment of I/R injury, prevention of IF/TA, minimization of immune suppression and reversal or stabilization of chronic transplant inflammation and fibrosis as recently reviewed [22]. Ongoing immune injury to the graft may be caused by cellular and/or humoral mechanisms accompanied by de novo donor specific antibody (DSA) formation [23-25]. The importance of these de novo DSA as a major cause of allograft failure in the long term has recently been confirmed in numerous studies [23,25]. Importantly, it was shown that DSAs with the ability to activate complement, as determined by binding of C1q, are associated with greater risk of acute rejection and allograft loss [24]. By their immunosuppressive properties, MSCs may possibly serve an important role to control lymphocyte and antibody induced damage to the kidney.

In a rat heart transplantation model donor MSCs suppressed allogeneic T-cell responses *in vitro* and *in vivo* and intravenous administration of MSCs prolonged the survival of transplanted hearts, possibly by induction of allograft tolerance through changing the Th1/Th2 balance [26]. Interestingly, a recent study showed that heart grafts, which were tolerized through third-party multipotent adult progenitor cells, could be retransplanted to secondary hosts without immunosuppression [27]. In a study by Casiraghi et al., pre transplant infusion of MSCs prolonged the survival of semi-allogeneic (B6C3 in B6) murine heart transplants through the generation of regulatory T cells. A single recipient-derived MSC infusion given peri transplant was marginally effective, and a single MSC dose given one day after transplantation was not effective at all, emphasizing the importance of timing. The same group investigated the optimal timing for MSC infusion to promote immune tolerance in a murine kidney transplant model [28]. Pre-transplant MSC infusion induced a significant prolongation of kidney graft survival by inducing T regs [28], however post-transplant infusion caused premature graft dysfunction and failed to prolong graft survival. These results suggest that the inflammatory milieu is of importance for the mechanistic function of MSCs.

Two experimental studies are of particular interest for our clinical protocol. After kidney transplantation, Franquesa et al. observed a therapeutic effect of MSCs attenuating the progression of IF/TA when this process was already in progress [17]. Besides a reduction in IF/TA, MSC-treated animals demonstrated fewer macrophages infiltrating the parenchyma, lowered expression of inflammatory cytokines in combination with increased expression of anti-inflammatory factors [17]. In another experimental model, the combination of mTOR inhibitor and MSCs was shown to attenuate alloimmune responses and to promote allograft tolerance in heart transplants [29]. Indeed, combination therapy of MSCs and low-dose mTOR inhibitor rapamycin achieved long-term heart graft survival (>100 days) with normal histology. The treated recipients did accept donor skin grafts but rejected third-party skin grafts, indicating the establishment of donor specific tolerance. Tolerant recipients exhibited neither intragraft nor circulating DSA, but demonstrated significantly higher frequencies of both tolerogenic dendritic cells (Tol-DCs) and CD4^+^CD25^+^Foxp3^+^T cells in the spleens [29].

A limited number of clinical studies have investigated the role of MSCs in the transplant setting. Two studies have focused on the role of MSCs in the early induction phase. In a pilot study of safety and clinical feasibility, autologous MSCs were tested in renal transplant recipients. MSC infusion was shown to be feasible, allowing an increase of T-reg in the peripheral blood and control of memory CD8^+^T cell function [30]. In these patients, timing of the infusion seemed of major importance. Administration of MSC in the early phase after transplantation negatively affected kidney graft function, which was not the case when MSCs were administered before transplantation [31]. In a trial among 159 patients undergoing renal transplantation, the use of autologous MSCs compared with anti-IL-2 receptor antibody induction therapy resulted in lower incidence of acute rejection, decreased risk of opportunistic infection and better estimated renal function at 1 year [32]. Moreover, in a clinical pilot study allogeneic MSCs were administered in 6 renal transplant recipients. Allogeneic donor derived MSCs combined with low dose tacrolimus was safe and prevented acute rejection after renal transplantation [33], however immune monitoring was not performed in this study.

In our phase 1 clinical study safety and feasibility of autologous MSC therapy was tested in HLA-DR mismatched patients with subclinical rejection (SCR) in their renal biopsy at 4 or 24 weeks after renal transplantation [34,35]. In total 6 patients received MSC infusion which was feasible and well tolerated without adverse events related to the treatment itself. In addition, initial results suggested immune suppression after MSC therapy. All patients that received MSCs demonstrated a profound reduction in proliferation of patient peripheral blood mononuclear cells (PBMCs) 12 weeks after MSC infusion upon stimulation with donor specific PBMCs, while the response to third party PBMCs was more variable. Three patients developed opportunistic viral infections, which might have been related to the MSC treatment. In 2 patients with allograft rejection the infiltrate had disappeared after the MSC infusion. In addition, in patients diagnosed with IF/TA, the areas of IF/TA disappeared after treatment with MSCs, indicating that MSCs might play a role as antifibrotic and reparative treatment, which is one of the objectives in the current study. Effects of MSC therapy in cardiovascular disease have not been studied in previous clinical trials in renal transplant recipients.

## Methods and design

### Objectives and endpoints

The primary end point of the current study is the level of fibrosis, as determined by quantitative Sirius Red (SR) scoring of biopsies of MSC treated and untreated groups at 6 months compared to 4 weeks post transplantation. Other endpoints include: composite endpoint efficacy failure (Biopsy Proven Acute Rejection (BPAR), graft loss) at 6 months; renal function measured by eGFR (MDRD formula and iohexol clearance) and proteinuria at 6 months; cytomegalovirus (CMV), BK infection (viremia, disease and -syndrome) and other opportunistic infections; adverse events; the presence of DSA and other phenotypical and functional aspects of the donor specific immune response; to compare the progression of “subclinical” cardiovascular disease in the different treatment groups by assessing echocardiography.

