**Figure 1 Fig1:**
[figure not shown]
**Study scheme.** In total 70 patients will be included in the study, 18–75 years old. Patients will be randomised prior to transplantation. Thirty five of these patients will be included in the Certican®/MSC group and 35 patients in the Certican®/standard dose tacrolimus group. All patients will receive steroids (100 mg at day 1 to 3, 50 mg at day 4, 20 mg at day 5 to 15, 15 mg at day 15 to 21, and 10 mg after day 22) and induction treatment with alemtuzumab at day 0 and 1 (15 mg subcutaneously)*. Certican® dose will be 1.5 mg b.i.d. with trough levels between 3 and 8 ng/ml. Tacrolimus will be started orally 3 h before surgery (initial dose 2x5 mg ). In the first 6 weeks target trough levels are aimed at 10 ng/ml (range 8 to 12 ng/ml) for tacrolimus and thereafter 6–8 ng/ml. In the MSC treated group, BM will be harvested just prior to the renal transplantation and MSCs will be cultured in the GMP laboratory. Patients will receive 2 doses of a target of 1,5x10^6^ autologous BM MSCs per/kg body weight IV (range 1-2x10^6^) 7 days apart, 6 and 7 weeks after transplantation. The dose of tacrolimus will be reduced to 50% at the time of the second MSC infusion and completely withdrawn 1 week later. Patients will receive at that time point 15 mg of prednisolone. In all patients a renal biopsy will be performed at 4 weeks and at 6 months and scored according to the Banff criteria.

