### Fibrosis scoring by renal biopsy

A standard renal protocol biopsy is performed prior to the transplantation and at 6 months after transplantation. At 4 weeks after transplantation a study biopsy is taken to assess the renal histology before MSC infusion. Biopsies are scored according to the Banff criteria and processed for immunohistochemistry (HE staining; staining for CD3, CD4, CD68, FOXp3, C4d and CD20). In addition, the amount of cortical collagen (SR-positive area) will be measured and finally expressed as the percentage of the total analyzed cortical surface. Moreover, changes in mRNA expression of pro- and anti-fibrotic genes (including FGFb and fibronectin) in renal biopsies taken before and after MSC infusion through real-time quantitative PCR will be performed.

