### Sample size calculation

In our study a sample size of 25 in each group (or 50 in total) will have a 80% power to detect a difference in mean percentages of fibrosis of at least 25% using a two group t-test with a 0.05 two-sided significance level (alpha). In this calculation we used the following assumptions: we expect the control group (no MSC’s) to have a mean percentage of fibrosis of 18% at 6 months [38-43]. We assume that both groups show equal variability in measured fibrosis and that the common standard deviation is 5% [40]. A mean percentage of 14% in MSC group (25% less fibrosis) is considered a clinically relevant difference. We anticipate that 70% of included patients will have valid measurements (withdrawal included). We therefore plan to include 70 patients in total, 35 in the MSC group and 35 in the control group.

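### The primary endpoint compares month 6 with week 4, but the trial is powered on unadjusted month-6 means; a month-6 analysis adjusted for baseline fibrosis would resolve this and gain power

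*Protocol article*

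**What the plan says.** The Objectives and endpoints section gives the primary endpoint as fibrosis by "quantitative Sirius Red (SR) scoring of biopsies of MSC treated and untreated groups at 6 months compared to 4 weeks post transplantation". The Abstract and the Discussion word it in the same way. Week 4 is the only reference biopsy named.

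The section on fibrosis scoring describes three biopsies. Two are routine: "A standard renal protocol biopsy is performed prior to the transplantation and at 6 months after transplantation". The third is taken for the trial: "At 4 weeks after transplantation a study biopsy is taken to assess the renal histology before MSC infusion". Table 1 marks all three. Sirius Red measurement is described without leaving out the pre-transplant core: "the amount of cortical collagen (SR-positive area) will be measured and finally expressed as the percentage of the total analyzed cortical surface". No section gives that core a part in the primary comparison.

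The Sample size calculation section works with month-6 levels: 18% in controls, 14% with MSCs, common SD 5%. It states that "a sample size of 25 in each group (or 50 in total) will have a 80% power", "using a two group t-test with a 0.05 two-sided significance level (alpha"). No week-4 value enters. On losses it says "We anticipate that 70% of included patients will have valid measurements (withdrawal included"), without saying which biopsies must be valid, and so plans 35 patients per arm.

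The Figure 1 legend adds: "Patients will be randomised prior to transplantation". The week-4 biopsy therefore comes after randomisation but before the first infusion at week 6.

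**The concern.** The endpoint and the calculation that justifies 70 patients describe different quantities. One is a comparison with week 4. The other is a month-6 level.

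The natural reading of the endpoint is a within-patient change. A change needs a valid core at both visits and carries the sampling error of both. Whether it is more or less precise than the month-6 level depends on the correlation between the biopsies, which the article does not give. The plan has no spare power to absorb a less precise analysis.

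The data already scheduled would support a better analysis. Adjusting the month-6 value for earlier fibrosis removes variance that subtraction may add, and it does not require every patient to have both cores.

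**Working it through.** **Inputs from the Sample size calculation section.** Difference 18 − 14 = 4 points; SD 5; two-sided alpha 0.05; 70% of 35 per arm valid, so 0.70 × 35 = 24.5 per arm.

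**Reproducing the plan.** The normal approximation gives 25 per arm (power 80.7%). The exact t-test gives 79.1% at 25 per arm. Inflation: 50 / 0.70 = 71.4, against 70 planned. At 24.5 per arm, t-test power is 78.3%. The 4-point difference is the one used: a full 25% reduction from 18% would be 4.5 points and need about 20 per arm.

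**Assumptions not in the documents.** SD 5 at week 4 as well as at month 6; correlation r between the week-4 and month-6 values; no expected difference between arms at week 4, so that the effect on the change is also 4 points. The power figures ignore the one or two degrees of freedom spent on covariates.

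**Formulas.**
- Change from week 4: SD = 5 × √(2(1 − r))
- Month 6 adjusted for week 4: residual SD = 5 × √(1 − r²)
- Unadjusted month 6: SD = 5

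The change has the same SD as the unadjusted level when 2(1 − r) = 1, that is, at r = 0.5. Below that it is less precise.

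**Power at 24.5 per arm, difference 4** (unadjusted month 6: 78.3% throughout):

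| r | SD of change | Power, change | Residual SD, adjusted | Power, adjusted |
|---|---|---|---|---|
| 0.3 | 5.92 | 64.0% | 4.77 | 82.0% |
| 0.4 | 5.48 | 70.7% | 4.58 | 84.9% |
| 0.5 | 5.00 | 78.3% | 4.33 | 88.6% |
| 0.6 | 4.47 | 86.6% | 4.00 | 92.9% |
| 0.7 | 3.87 | 94.3% | 3.57 | 97.0% |

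The adjusted analysis is the more powerful of the two at every correlation shown.

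**Adding the pre-transplant value.** With correlations r1 (week 4 with month 6), r2 (pre-transplant with month 6) and r12 (between the two earlier values), the share of variance explained is (r1² + r2² − 2·r1·r2·r12) / (1 − r12²). At r1 = r2 = 0.4 and r12 = 0.5 this is (0.16 + 0.16 − 0.16) / 0.75 = 0.213, and power rises from 84.9% to 87.1%. With r1 of 0.3, 0.5 or 0.6, r2 from 0.2 to 0.5 but no higher than r1, and r12 of 0.3 or 0.5, the gain runs from about 0 to 5 points (largest: 88.6% to 93.8%).

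**If only complete pairs were analysed.** Suppose the 70% covered month-6 cores alone and a further 5%, 10%, 15% or 20% lacked a valid week-4 core. That leaves 23.3, 22.1, 20.8 or 19.6 per arm. Power for the change at r = 0.5 would then be 76.1%, 73.7%, 71.2% or 68.4%. If the 70% already means both cores, nothing further is lost. The article does not say which applies.

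**The case against.** **The article prescribes no change score.** It names no model and no analysis set. The one test it names needs only the month-6 core, and an analysis plan not shown here may already adjust for baseline. This stands as a limit: the loss of power is conditional on a change analysis. It does not remove the point, because the article itself fixes a reference visit for the endpoint and a test that ignores that visit.

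**Week 4 is a reasoned baseline.** It precedes infusion and follows the injury of transplantation. Until the infusions, bone marrow harvest is the only difference between the arms that the article describes. This stands too, and week 4 should remain the main covariate. The pre-transplant core's own merit is that it is untouched by anything that follows transplantation.

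**Stronger readings are tempting but unsupported.**
- A reader might infer that patients without a valid week-4 core are dropped. No exclusion of that kind is written, and the 30% allowance may already cover failed week-4 cores.
- A reader might infer that, in an open-label trial, the extra biopsy will be declined unevenly by arm. No refusal or failure rate is given for either arm, and the Figure 1 legend plans the biopsy in everyone.
- A reader might conclude that the pre-transplant core is wasted. Nothing prevents its use, and its own contribution to power is small.

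**Conclusion.** The point holds as a mismatch between endpoint and calculation for which a better analysis is available from data already scheduled. Analysed as a change from week 4, the endpoint has less power than planned whenever the correlation between biopsies is below about 0.5: 64% at 0.3 and 71% at 0.4, against 78.3% for the unadjusted month-6 comparison. Above 0.5 the change does better than the unadjusted comparison, but it remains behind the adjusted analysis. Adjusting for week 4 gives 82%, 85% and 89% at correlations of 0.3, 0.4 and 0.5.

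Most of the gain comes from adjusting instead of subtracting. The pre-transplant value contributes about 0 to 5 points, and its further use is to keep patients whose week-4 value is missing. All correlations are assumed, as is an SD of 5 at both visits. The number of patients who would be kept cannot be computed from the documents.

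**What to change.** Before any analysis by arm, state the following in the protocol or analysis plan:

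1. The primary analysis is a linear model of the month-6 Sirius Red percentage, with arm, week-4 Sirius Red and pre-transplant Sirius Red as terms.
2. It includes every randomised patient with a valid month-6 core.
3. A missing or inadequate week-4 value is filled in from the pre-transplant value, using neither arm nor outcome.
4. The change from week 4 to month 6 is reported as supportive.
5. The 70% allowance is defined as the share of patients with a valid month-6 core, so that the sample size and the analysis refer to the same patients.

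The cost is wording, two degrees of freedom and, if not already planned, Sirius Red image analysis of pre-transplant cores taken as routine. No further biopsy is needed.
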